**Discussion/conclusion:**

This trial allows for a comparison between day-case and inpatient stapes surgery to investigate the hypothesis that day-case stapes surgery is associated with a higher quality of life and higher cost-effectiveness, while maintaining equal hearing results, compared to inpatient stapes surgery.

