### Sample size calculation and recruitment

To establish equivalence in postoperative mean air conduction of 5 dB (standard deviation 10) between the day-case and the inpatient group with an alpha of 0.05 and a power of 80 %, 51 participants per group are needed. To anticipate on a withdrawal of 10 % of the participants, 5 more participants than needed will be recruited per group. At the ENT department in UMC Utrecht, we perform an average of 80 (revision) stapedotomies per year. Assuming a participation rate of 75 %, we will be able to include the necessary number of 112 patients in two years. If participants wish to leave the study or the investigator decides to withdraw a participant from the study for urgent medical reasons, these participants will not be replaced unless these account for more than 10 %.

Patients will be recruited from the outpatient ENT department of the UMC Utrecht. If an otosclerosis patient meets the criteria for stapes surgery and the inclusion criteria for this study, one of the researchers will explain the content of the study and provide the patient with written patient information and an informed consent form. Patients consent to the use of their data for the research purposes outlined in this protocol, which includes publication of the results once the trial has been completed. Further details can be found in Additional file 1 (informed consent form; translated to English, original in Dutch). Patients that do not want to be included in the study because they want to undergo stapes surgery in a clinical setting will be asked whether they want to fulfill the study procedures and whether their data can be used for analysis.

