### Cost-effectiveness/utility analysis

The difference in costs and benefit will be represented using the Incremental Cost Utility/Effectiveness Ratio (ICUR/ICER). The ICUR/ICER is calculated by dividing the difference in costs by the difference in utility or effectiveness. Effectiveness will be reflected by pure-tone audiometric results. Utility reflects the amount of money that people are willing to pay to achieve a certain health status. Utility scores derived from questionnaires such as the EuroQoL-5D and the Health Utilities Index 3 can be used to calculate the ICUR.

Participants will be asked to keep a costs diary. Participants will fulfill this diary preoperatively and at regular intervals postoperatively. The first month the diary will be fulfilled weekly followed by monthly fulfillment for the duration of one year. Costs will be measured from a societal and health care perspective. Both direct and indirect costs will be collected. Direct costs include hospitalization, surgery, doctor’s visits, and diagnostic tests. Indirect costs include travel expenses and sick leave. The Dutch guidelines for costing research in health economic evaluations, issued by the National Healthcare Institute [36], will be used to calculate unit prices of resources that were used.

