## Discussion/conclusion

Stapes surgery seems to be a surgical procedure that is well suited for day-case treatment as it has proven to be a safe treatment with low complication rates. However, current literature lacks evidence based recommendations supporting day-case stapes surgery. This randomized controlled trial allows for a comparison between day-case and inpatient stapes surgery to investigate the hypothesis that day-case stapes surgery is associated with a higher QoL and higher cost-effectiveness, while maintaining equal hearing results, compared to inpatient stapes surgery. This is the first high quality trial evaluating and quantifying the benefits of day-case stapes surgery for patients with otosclerosis.

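### The hearing-based ICER divides by a difference the trial expects to be zero, so if the hypothesis holds, its size and sign are mostly noise

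*Protocol article*

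**What the plan says.** The section on cost-effectiveness/utility analysis names the ICUR/ICER as the way costs and benefit will be presented together, and defines it: "The ICUR/ICER is calculated by dividing the difference in costs by the difference in utility or effectiveness". It then fixes the denominator of the ICER: "Effectiveness will be reflected by pure-tone audiometric results". For the ICUR the wording is looser: "Utility scores derived from questionnaires such as the EuroQoL-5D and the Health Utilities Index 3 can be used to calculate the ICUR".

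On hearing, the abstract's conclusion expects a benefit from day-case surgery "while maintaining equal hearing results, compared to inpatient stapes surgery", and the main discussion repeats this. The sample size section starts from the same idea: "To establish equivalence in postoperative mean air conduction of 5 dB", with an SD of 10 dB and 51 participants per group. On the other outcomes, the discussion hypothesises that "day-case stapes surgery is associated with a higher QoL and higher cost-effectiveness".

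**The concern.** The article commits to a ratio and, for its ICER, puts in the denominator the one quantity that the trial hopes to show is no different between groups. A ratio whose denominator is centred on zero has no finite mean or variance, and its sign follows the chance sign of the denominator.

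The sign is also ambiguous. With hearing gain coded so that positive is better, cheaper-and-better and dearer-and-worse both give a negative ratio, while cheaper-but-worse and dearer-but-better both give a positive one.

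Higher cost-effectiveness is one of the trial's stated hypotheses. If hearing proves equivalent, as hoped, the hearing-based ICER can neither support nor refute it. Two trials with the same cost saving could report very different ratios of opposite sign.

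**Working it through.** **Inputs.** SD 10 dB, margin 5 dB, alpha 0.05, power 80% and 51 per group (56 with the withdrawal allowance), all from the sample size section. Expected hearing difference 0 dB, from the abstract and discussion. The article gives no cost figure, so none is used below.

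**The plan's own figure.** With one-sided alpha 0.05, the normal approximation gives 2 × [10 × (1.645 + 0.842)/5]² ≈ 49.5, so 50 per group. The one-sided t-test has power 0.799 at 50 and 0.806 at 51, which reproduces 51. This only confirms that the inputs are read correctly. Whether a one-sided calculation suits an equivalence aim is a separate question.

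**Precision of the ICER denominator.** SE = SD × √(2/n) = 10 × √(2/51) = 1.98 dB. With all 56 per group it is 10 × √(2/56) = 1.89 dB.

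**Size of the observed difference if hearing is truly equal.** P(|d| < c) = 2Φ(c/1.98) − 1:
- c = 0.5 dB: 20%
- c = 1 dB: 39%
- c = 2 dB: 69%

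For any fixed saving S, the absolute ICER therefore exceeds S/0.5 = 2S per dB in 20% of trials and falls below S/2 = 0.5S per dB in 100 − 69 = 31%. The same saving gives ratios at least fourfold apart by chance alone. Holding S fixed leaves out cost variability and any correlation between cost and effect.

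**Sign and interval.** The chance that the observed difference has the wrong sign is Φ(−δ/1.98) for a true difference δ. The 95% Fieller set for the ratio is bounded only when the denominator differs from zero at the two-sided 5% level, so P(unbounded) = 1 − P(denominator significant). With a t distribution on 100 degrees of freedom:

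| True difference | Denominator significant | Fieller set unbounded | Wrong sign |
|---|---|---|---|
| 0 dB | 5.0% | 95% | sign is 50/50 |
| 2.5 dB | 24.0% | 76% | 10% |
| 5 dB | 70.6% | 29% | 0.6% |

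**Does a larger sample help?** Not under the trial's hypothesis. At a true difference of zero the first row is the same for every sample size. With 56 per group the unbounded share is about 74% at 2.5 dB and 25% at 5 dB (normal approximation).

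**Contrast with net monetary benefit.** This is λ × (effect difference) − (cost difference), for a threshold λ. With an effect difference of 0 and a saving S it equals λ × 0 − (−S) = S. It stays finite and interpretable exactly where the ratio breaks down.

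**The case against.** The strongest reply is that the article plans two ratios. The ICUR uses utilities, and the trial hypothesises higher quality of life with day-case surgery, so that denominator is not expected to be zero. This stands. A reader might infer that the whole economic evaluation fails if hearing is equal. The documents do not support that, and the point is confined to the hearing-based ICER. It survives the limit because the audiometric effect measure is the firmer commitment in the wording, and because the article gives no expected utility difference or SD that would show the ICUR to be stable.

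Other objections, and what remains of them:
- **Uncertainty methods may sit in the full protocol or analysis plan.** True, so the absence of a bootstrap or acceptability curve is not counted as an error. The point concerns the effect measure that the article does fix.
- **The statistical analysis section promises between-group mean differences with 95% intervals.** A reader would therefore see a near-zero hearing difference directly. That softens the harm but does not make the ratio informative.
- **No decision rule is attached to the ratio, and cost-effectiveness is secondary.** Also true. The ICUR and ICER are nevertheless the only joint summaries of cost and benefit that the section names.
- **The 95% figure is simply 1 minus alpha.** Correct: it holds for any denominator that is truly zero. The 76% and 29% figures do depend on the plan's SD and sample size.
- **The ICER would be undefined.** A reader might infer this, but it applies only at an observed difference of exactly zero. The practical problem is instability.
- **Raw thresholds, where lower is better, would reverse the sign.** This is conditional, since the section does not say how the audiometric result is coded.

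**Conclusion.** The concern holds for the hearing-based ICER and not for the ICUR. If the trial's own hypothesis of equal hearing is true, the ICER's sign is 50/50 and its 95% Fieller set is unbounded in 95% of trials. The set remains unbounded in 76% at a true difference of 2.5 dB and in 29% at the full 5 dB margin.

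These figures assume that effectiveness is postoperative mean air conduction with the SD of 10 dB used for the sample size, and 51 analysed per group. Another audiometric measure would change the standard error, but not the result at a true difference of zero.

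The primary hearing analysis is unaffected. The change should be made because it bears on a headline hypothesis and costs little.

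**What to change.** In the section on cost-effectiveness/utility analysis:

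- Make the utility-based analysis the main economic result.
- Report the cost difference and the effect differences separately, each with a bootstrap 95% interval, and show their joint bootstrap distribution on the cost-effectiveness plane.
- Base conclusions on incremental net monetary benefit over a stated range of thresholds, with an acceptability curve, and not on the hearing-based ratio. This also protects the utility analysis should the utility difference prove small.
- State the hearing effect as dB gained at 12 months, with positive meaning better, to match the one-year cost diary.
- Treat any hearing-based ICER as descriptive only, and show the quadrant in which it falls. Do not make its reporting depend on a significant denominator, since that would select large observed differences.

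The cost is revised analysis wording, a threshold range that has to be named, and a short bootstrap programme. No new data or participants are needed.

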### Statistical analysis

Baseline characteristics per group will be described as means and standard deviations. Differences in the baseline will be analyzed using the independent samples students *t-*test or non-parametric tests for continuous variables and the Fisher’s exact test for categorical variables.

The primary and secondary outcome data are quantitative and will be presented both continuous and categorical. Between-group mean differences, rate differences and rate ratios with 95 % confidence intervals will be calculated. For further analysis of between-group differences in both primary and secondary outcomes the independent samples students *t–*test or non-parametric tests will be used for continuous outcomes and the Fisher’s exact test for categorical outcomes. Within-subject comparisons will entail differences in mean values and percentages before and after stapes surgery. These will be analyzed using paired *t*-tests for continuous measures and the McNemar test for categorical outcomes.

Missing values will be handled using multiple imputation and all analyses will be performed on an intention-to-treat basis. A sensitivity analysis will be performed using all of the data acquired from patients that opted not to be included in the study, but did fill out the questionnaires and underwent pure-tone audiometric and speech audiometric follow-up.

The data will be reported according to the CONSORT Statement [37, 38].

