### Randomization, blinding and treatment allocation

A web-based randomization program (Julius Center, UMC Utrecht, Utrecht, The Netherlands) shall be used to allocate subjects randomly into two groups with stratification for age. Block randomization will be used with an allocation ratio of 1:1. The randomization chart, including block size, is established before the start of the study by an independent data manager and will not be available to any of the people involved with enrolment or treatment of participants. Consequently, treatment allocation sequence is concealed for participants, care providers and researchers. Blinding of both participants and care providers is not possible, since both participants and care providers will be aware of the surgical setting and hospital stay.

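### The primary outcome is given both a continuous test and, in categorised form, Fisher's exact test, with neither named as decisive, although only the mean difference in dB can be judged against the 5 dB margin

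*Protocol article*

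**What the plan says.** Under Sample size calculation and recruitment, the trial is sized on one continuous quantity: "To establish equivalence in postoperative mean air conduction of 5 dB", with an SD of 10, "with an alpha of 0.05 and a power of" 80%. The result is that "51 participants per group are needed". The section Primary outcome measure names postoperative air conduction at about two and twelve months, averaged over four frequencies.

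The Statistical analysis section does three things that bear on this outcome:

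- It states the form of the data: "The primary and secondary outcome data are quantitative and will be presented both continuous and categorical".
- It plans mean differences, rate differences and rate ratios, each with a 95% confidence interval.
- It then assigns tests, as further analysis, to primary and secondary outcomes alike. These are the t-test or a non-parametric test for continuous outcomes, and Fisher's "exact test for categorical outcomes".

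The section does not rank the two forms of the primary outcome, and it does not mention the 5 dB margin.

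**The concern.** Taken together, these sentences give mean air conduction two difference tests at each visit, one in dB and one on proportions. The design rests on the first scale only. A margin of 5 dB has no direct meaning for the share of patients below a threshold, so the categorical result cannot answer the question for which the trial was sized.

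The direction of the risk matters. The Discussion gives the hypothesis as better quality of life and cost-effectiveness with hearing results that stay equal. A difference test with little power tends to come out non-significant, and in such a trial that is easily read as support. If the two forms disagree, nothing in the section says which one to believe. The less sensitive one is also the one more likely to look like equal hearing.

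**Working it through.** **Inputs.** From Sample size calculation and recruitment: difference 5 dB, SD 10, alpha 0.05 (sidedness not stated), power 80%, 51 per group. From Randomization, blinding and treatment allocation: 1:1. Assumed here: normal data, equal SDs, one visit, two-sided 5% tests. The cut-offs are also assumptions, and a range is shown.

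**Step 1: the plan's own figure.** For two means, n per group = 2 × [SD × (z₁₋α + z₁₋β) / difference]².

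- One-sided 0.05: 2 × [10 × (1.645 + 0.842) / 5]² = 49.5, so 50. With the t distribution, power is 79.9% at 50 and 80.6% at 51, which gives the stated 51.
- Two-sided 0.05: 2 × [10 × (1.960 + 0.842) / 5]² = 62.8, so 63. This does not match.
- Two one-sided tests for equivalence at 0.05 each, true difference zero: 2 × [10 × (1.645 + 1.282) / 5]² = 68.5, so 69. This does not match.

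The stated 51 therefore reproduces as a single one-sided t-test on the mean in dB. No categorical calculation is involved.

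**Step 2: the continuous test at a true 5 dB shift.** The standard error is 10 × √(2/51) = 1.98 dB, so the noncentrality is 5 / 1.98 = 2.52 on 100 degrees of freedom. The two-sided 5% t-test then has power 0.706, or 71%.

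**Step 3: Fisher's test on the same data, dichotomised.** If a share p of inpatients lies below the cut-off and the day-case mean is 5 dB (0.5 SD) worse, the day-case share is Φ(Φ⁻¹(p) − 0.5). Power comes from enumerating both binomials with n = 51 and adding up the outcomes with a two-sided exact p-value of at most 0.05.

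| Cut-off | Inpatient share below | Day-case share below | Fisher power |
|---|---|---|---|
| Midway between the group means | 59.9% | 40.1% | 47% |
| 5 dB above midway | 77.3% | 59.9% | 40% |
| 10 dB above midway | 89.4% | 77.3% | 28% |
| 90% of inpatients below | 90% | 78.3% | 27% |

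With 50% of inpatients below the cut-off, the day-case share is Φ(−0.5) = 30.9% and power is 44%. Over inpatient shares of 50% to 90% the range is thus about 27% to 47%. Fisher's test misses a shift as large as the whole margin in 53% to 73% of trials (1 − 0.47 and 1 − 0.27). The t-test misses it in 29% (1 − 0.71). The range is not a worst case: a simulation with the cut-off 10 dB below the inpatient mean gave 19%.

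**Step 4: how often the two tests differ.** In 20,000 simulated trials with the cut-off at the inpatient mean, the tests disagreed in about 30% at a true 5 dB shift and 16% at 2.5 dB. At 5 dB, about 28 of those 30 points were a significant t-test with a non-significant Fisher test. This largely restates the power gap, but it shows which way a conflict would run.

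**The case against.** The strongest reply is that the categorical form was never meant to decide anything. The article speaks of presenting the data both ways and introduces the tests as further analysis, after the estimates with intervals. The sample size and the definition of mean thresholds both point to the mean in dB as the lead form. The testing sentence covers all outcomes at once and can be read as a generic match of test to data type. Some other outcomes do have categories, such as sensorineural hearing loss and the graded dizziness handicap. Much of this stands. A reader might infer that the plan sets up a second, competing verdict on the primary outcome; the text does not go that far, since it nowhere gives Fisher's test authority over the primary question. What remains is that the sentence explicitly includes the primary outcome and leaves the two forms unranked.

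A reader might also object that no cut-off for air conduction is given and that one could be picked after the data are seen. The documents do not support this as a finding. An article commonly leaves category boundaries to the full protocol or analysis plan, which are not shown here, and nothing suggests a choice among several cut-offs after the fact.

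Thirdly, the missing link to 5 dB is not peculiar to Fisher's test. The t-test and the non-parametric tests are difference tests too, and a non-significant t-test would not show equivalence either. That stands in full. The two forms still differ in one respect: the mean difference and its interval can be set against 5 dB, and the proportions cannot.

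**Conclusion.** The point holds in a limited form. The trial is sized on equivalence in mean air conduction. The analysis section assigns the primary outcome a continuous difference test and, in categorised form, Fisher's exact test. It does not say which carries the conclusion, and it ties neither to the margin. At a true 5 dB shift with 51 per arm, Fisher's test has about 27% to 47% power against 71% for the two-sided t-test, so its non-significance is no evidence that hearing is equal. These figures assume normal data, an SD of 10 and cut-offs with 50% to 90% of inpatients below them.

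The losses in power would harm the primary conclusion only if the categorical result were used for it, which the article neither states nor rules out. That makes this a correction worth making rather than a fatal flaw.

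**What to change.** In the Statistical analysis section, state that the primary conclusion rests only on the between-group difference in mean air conduction in dB, with its confidence interval compared with the 5 dB margin. State that categorised air conduction is supportive, reported through the rate differences and rate ratios with 95% intervals that are already planned. A Fisher p-value on it should not be used to claim or deny equal hearing.

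This takes one or two sentences and no new patients or measurements, and the article says recruitment is still under way. The direct cost is that the categorical p-value no longer counts towards the primary question.

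One consequence should be faced when the sentence is written. If the true difference is zero and 51 per arm are analysed, the interval falls wholly within ±5 dB in about 61% of trials at 0.05 on each side (a 90% interval). At 0.025 on each side (a 95% interval) the figure is about 41%. The interval level should therefore be fixed in the same sentence. The shortfall against 80% comes from the sample size and not from this change.

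### The trial is sized for equivalence within 5 dB, but the only tests named for the primary outcome test for a difference, and no rule links the planned confidence interval to the margin

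*Protocol article*

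**What the plan says.** The Sample size section of the protocol article gives the aim as "To establish equivalence in postoperative mean air conduction of 5 dB". It assumes an SD of 10 dB, sets the error rates in the words "with an alpha of 0.05 and a power of 80" (per cent), and concludes that "51 participants per group are needed". Five more per group are added for withdrawal, making 112 in all. The Abstract's closing paragraph and the Discussion put the hearing hypothesis in the same spirit: day-case surgery should do better on quality of life and cost-effectiveness "while maintaining equal hearing results".

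The Statistical analysis section first plans mean differences between the groups with 95% confidence intervals. It then turns to testing, in a sentence that opens "For further analysis of between-group differences in both primary and secondary outcomes the independent samples students". The Student's test is thus the first option, and the alternative is given in the phrase "or non-parametric tests will be used for continuous outcomes". The same wording covers primary and secondary outcomes. The 5 dB figure appears only in the sample size paragraph. The article states no equivalence test and no criterion for concluding equivalence.

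**The concern.** A t-test or rank test asks whether the data contradict a difference of zero. The hearing hypothesis needs the opposite: data that contradict a difference as large as 5 dB. Failing to reject zero is weak evidence for that, and it becomes easier as the data become noisier. A larger SD, poor audiometry or more missing data would each make a non-significant result more likely.

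The planned 95% interval is the right raw material, but without a stated rule the reader does not know what result would count as equal hearing. The non-parametric option adds a smaller mismatch, because the p-value of a rank test does not address a margin set on mean dB.

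At stake is the trial's central claim, that earlier discharge costs nothing in hearing.

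**Working it through.** **Inputs** (Sample size section): margin 5 dB, SD 10 dB, alpha 0.05 with sidedness not stated, power 80%, 51 per group (56 with the withdrawal allowance). Allocation is 1:1 (Randomization section).

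**1. Reproducing the plan's figure.** The formula is n per group = 2 × SD² × (z_alpha + z_power)² / margin² = 8 × (z_alpha + z_power)².
- Single one-sided test at 0.05: 8 × (1.645 + 0.842)² = 49.5, so 50; the exact noncentral-t calculation gives **51**, the plan's figure.
- Two-sided difference test at 0.05: 8 × (1.960 + 0.842)² = 62.8, so 63 (exact 64).
- Equivalence by two one-sided tests at 0.05 each, true difference 0: 8 × (1.645 + 1.282)² = 68.5, so 69 (exact 70).
- Equivalence at 0.025 each: 85 (exact 86).

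Of these, only the single one-sided test gives 51.

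**2. What each criterion accepts at 51 per group.** SE = 10 × √(2/51) = 1.98 dB, on 100 degrees of freedom.
- The two-sided t-test is non-significant if the observed difference is below 1.984 × 1.98 = **3.93 dB**.
- The 90% interval lies inside ±5 dB if the observed difference is below 5 − 1.660 × 1.98 = 5 − 3.29 = **1.71 dB**.
- The 95% interval lies inside ±5 dB if the observed difference is below 5 − 3.93 = **1.07 dB**.

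Observed differences from about 1.7 to 3.9 dB are therefore non-significant although equivalence is not shown by the 90% interval.

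**3. Error if the true difference is 5 dB.** The noncentrality is 5 / 1.98 = 2.52.
- Power of the two-sided t-test is 70.6%, so it is non-significant **29.4%** of the time. At 56 per group power is 74.6%, so 25.4%.
- Two one-sided tests at 0.05 declare equivalence **5.0%** of the time at 51 per group; the 95% interval rule does so 2.4% of the time.

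**4. Power of the margin-based rule at a true difference of 0** (integrated over the sampling distribution of the SD).
- 90% interval: 61% at 51 per group, 68% at 56, 80% at 70.
- 95% interval: 41% at 51, 49% at 56, 80% at 86.

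**5. Can a significant difference also satisfy equivalence?** This needs (1.984 + 1.660) × SD × √(2/51) < 5, so SD < 5 / (3.644 × 0.198) = 6.9 dB. At the planning SD of 10 it cannot happen with 51 per group.

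**The case against.** The strongest reply is that the plan already holds what an equivalence conclusion needs. It pre-states a 5 dB figure, it plans a 95% interval for the mean difference, and it introduces the tests only as further analysis. On that view one joining sentence is missing, and in a condensed article that sentence may stand in the registered protocol or an analysis plan. This has force. It rules out saying that the plan could never support its conclusion, and it makes the rank-test point secondary, since the mean difference and its interval remain whichever test is added. It does not remove the mismatch. The article is not silent on the primary test: it names difference tests and applies them to primary and secondary outcomes alike.

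A second reply concerns sidedness. The article prints no plus-or-minus sign, its objectives speak of effectiveness, and 51 per group matches a single one-sided test. Limits of -5 to +5 dB are therefore a reading of the word equivalence. That stands as an assumption. Under a one-sided reading the gap is the same, because the named tests still do not refer to 5 dB.

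Two stronger readings are tempting and are not supported:
- A reader might infer that the investigators intend to report a non-significant test as equal hearing. The article does not say so. The 29% figure is conditional on that use.
- A reader might infer that a precise trial with a trivial but significant difference would wrongly contradict equality. At the plan's own figures a significant result needs at least 3.93 dB, which puts the upper 90% limit at 3.93 + 3.29 = 7.2 dB or more, outside the margin. The conflict could arise only with an SD below about 6.9 dB.

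**Conclusion.** The point holds. The stated objective for the primary outcome is equivalence within 5 dB, the named tests address a different null, and no criterion connects the planned interval to the margin. This is a contradiction within the article, not a detail left to another document.

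If non-significance were used as the criterion, the chance of passing a true 5 dB difference as equal would be 29% at 51 per group and 25% at 56, about five to six times the 5% of two one-sided tests. This rests on SD 10 dB, normally distributed means, a two-sided margin and alpha 0.05 for each one-sided test. A larger SD would raise the 29%. The stated 80% power does not apply to two-sided equivalence at this sample size. It should be corrected before the final data are seen, and the article reports that recruitment is still under way.

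**What to change.** In the Statistical analysis section:
- Make the primary analysis the confidence interval for the mean difference in air conduction between the groups, judged against -5 to +5 dB. Conclude equivalence only if the whole 90% interval (two one-sided tests at 0.05) lies inside. Report the 95% interval beside it.
- State how the rule applies to the two primary time points, about two and twelve months: at both, or at one that is named in advance. Requiring both cannot raise power above that for either alone.
- State that a non-significant difference test is not evidence of equal hearing, and do not use a rank test for the primary conclusion.
- Keep difference tests for quality of life and costs, where the hypothesis is one of superiority.

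In the Sample size section, state whether the margin is two-sided, and restate the power under the adopted rule: about 61% with 51 analysed per group and 68% with 56, at a true difference of 0.

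The text change is a few sentences and needs no new data. The real cost is the disclosed loss of power. Restoring 80% under the 90% interval rule would take 70 analysed per group, or 140 in all. The article expects 80 × 0.75 = 60 participants a year, so that is 140 / 60 = 2.3 years of recruitment before any withdrawal allowance, against the two years planned. The sponsor can extend recruitment or accept the lower power openly.
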